### 2.3 Procedures

All procedures, including registration, consent, survey completion, and a two-week retest, administered to approximately 140 participants with mental disorders to evaluate the test–retest reliability of the five-item Japanese version of the Distress Questionnaire (DQ5-J), will be conducted online. Among retest completers, participants who report “no change” on the Patient Global Impression of Change at the two-week retest will be retained for the primary test–retest reliability analysis. Participation in the survey will be voluntary. Participants who complete the survey will receive points equivalent to 200 yen (approximately US $
1.30) and those who complete the retest will receive an additional 100-yen worth of points (approximately US $
0.65).

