### 2.4 Measures

The registry will incorporate standardized assessments of QOL and related psychosocial factors, psychiatric symptoms, sleep characteristics, and attitudes toward digital health technology. The following measures will be used. To measure QOL and related psychosocial factors, we will use the DQ5-J, six-item Kessler Psychological Distress Scale (K6) [40], EuroQoL 5 Dimensions 5-Level (EQ-5D-5L) [41,42], Satisfaction With Life Scale (SWLS), short form of the Metacognitions Questionnaire-Short Form (MCQ-30; only the positive beliefs about worry and the negative beliefs about uncontrollability and danger of worry subscales) [43,44], Effortful Control Scale (EC; only attention control subscale) [45,46], Cognitive Attentional Syndrome Scale-1 Revised (CAS-1R; only the coping strategies subscale) [47,48], Shift-and-Persist coping strategy (SAP) [49,50], subjective Socioeconomic Status (SES; childhood and current) [23,24,25], and the Brief Parental Burnout Scale (BPBs) [26]. To measure sleep characteristics, we will use the Insomnia Severity Index (ISI) [51,52], Regularity, Satisfaction, Alertness, Timing, Efficiency, Duration of Sleep Scale (RU-SATED) [53,54], Reduced Morningness–Eveningness Questionnaire (rMEQ) [55,56], Dysfunctional Beliefs and Attitudes about Sleep Scale (DBAS-16) [57,58], Ford Insomnia Response to Stress Test (FIRST) [59,60], Anxiety and Preoccupation about Sleep Questionnaire (APSQ) [61,62], Bedtime Procrastination Scale (BPS) [63,64], and Sleep Hygiene Practice Scale (SHPS) [65,66]. To measure psychiatric symptoms, we will use the Patient Health Questionnaire-9 (PHQ-9) [67,68], Generalized Anxiety Disorder-7 (GAD-7) [69,70], Liebowitz Social Anxiety Scale (LSAS) [71,72], Anxiety Sensitivity Index-3 (ASI-3) [38,73], Impact of Event Scale-Revised (IES-R) [74,75], Obsessive/Compulsive Inventory-Revised (OCI-R) [76,77], short form of the Autism-Spectrum Quotient (AQ-28) [78], and Adult ADHD Self-Report Scale (ASRS) [79]. To measure attitudes toward digital health technology, we will use the eHealth Literacy Scale (eHEALS) [80,81], Japanese version of the e-Therapy Attitudes and Process Questionnaire (eTAP-J) [82], and Attitudes toward Safety, Support, Understanding, and Risk for Human-AI therapists (ASSURE; two parallel scales: ASSURE-HT and ASSURE-AI), AI romance ethics, Anthropomorphism [83], Fulfilling emotional needs [84,85], Relationship Authenticity (RA) [86], and Desire for Real-World Relationships (DRR) [86]. Additionally, we will collect basic demographic characteristics, including age, sex, region of residence, occupation, marital status, fertility status, income status, and educational level. The survey consists of 1–40 items per page across 45 pages, and all items are mandatory.

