### 2.7 Statistical Analysis

To minimize information bias, we will conduct logic and range checks during data cleaning. Descriptive analyses will summarize distributions, floor and ceiling effects, and reliability indices. Unless otherwise specified, analyses will use two-sided tests, apply pre-specified multiple comparison correction strategies that differ by sub-study (see **Supplementary Materials**), and control for prespecified covariates (e.g., age and sex). Prespecified subgroup comparisons and corresponding interaction tests for diagnostic strata and sex will be conducted a priori, whereas other interaction analyses will be considered exploratory. Effect sizes with 95% confidence intervals will be reported, including Cohen’s *d *and Hedges’ *g* for continuous outcomes, odds ratios from logistic regression models, and standardized *β* coefficients for regression paths. Because the panel provider supplies only complete records for both the survey and the two-week retest, analyses will be restricted to complete-case data. Additional methodological details are provided in the **Supplementary Materials**.

In Sub-study 1a of Aim 1, all the analyses will be conducted in accordance with the Consensus-based Standards for the selection of health Measurement Instruments (COSMIN) guidelines [87]. The psychometric validation of the DQ5-J will include CFA to test the a priori unidimensional structure, with EFA reserved as a follow-up if the model fit is inadequate, internal consistency indices (Cronbach’s alpha and McDonald’s omega), test–retest intraclass correlation coefficients, model fit criteria, hypothesis-driven convergent and discriminant validity testing, and receiver operating characteristic analyses.

In Sub-studies 1b–1d of Aim 1, the correlations between the psychosocial factors and QOL/psychiatric symptoms will be examined by assessing the associations among the BPBs scores, SAP, SES, the psychiatric symptoms and sleep characteristics measures, and QOL using correlation analyses, linear regression models, and logistic regression. Sub-study 1d will additionally apply multiple-group structural equation modeling with moderated mediation and latent profile analysis to characterize the coping strategies assessed by the CAS-1R [88,89,90].

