### 2.8 Data Management and Quality Assurance

Data collection will be conducted through Macromill’s secure online research platform. At the beginning of the survey, participants will be presented with a pledge item asking them to commit to responding carefully, and only those who agree will be allowed to proceed to the subsequent questions [92]. The research team will receive only anonymized survey data from Macromill; no directly identifiable personal information (e.g., names, addresses, e-mail addresses, and contact details) will be provided. According to the company’s publicly available quality management policy, duplicate registrations using the same e-mail address or overlapping personal information are automatically rejected at the system level. Furthermore, during survey administration, the system identifies device cookies to prevent multiple submissions from the same terminal. Consequently, duplicate responses from the same individual are technically prevented. The survey interface requires the completion of all mandatory items and incorporates built-in logic and consistency checks to ensure data integrity. To enhance response quality, the survey platform automatically saves responses upon page transition, allowing participants to pause and resume at any point. To protect data validity, completion within 24-hours of survey initiation is required; surveys not submitted within this window are treated as withdrawal of consent and excluded from analysis.

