### 2.9 Ethics and Dissemination

The study protocol has received ethical approval from the relevant institutional review board (ID R07-137). Digital informed consent will be obtained from all participants before participation. The study findings will be disseminated through peer-reviewed publications, conference presentations, and plain-language summaries for participants and patient advocacy organizations.

The study has been registered in the Japan Registry of Clinical Trials (registration number: jRCT1030250737; registration link: https://jrct.mhlw.go.jp/latest-detail/jRCT1030250737; February 17, 2026). The registration includes the details of the study objectives, design, and data management procedures. Any protocol amendments will be reflected in updates to the records of the Japan Registry of Clinical Trials.

Participation in the study may involve temporary discomfort or psychological burden. Completion of the self-administered questionnaires (approximately 110 minutes in total) may impose a time burden on participants. Although no directly identifiable personal information will be collected, the risk of data breaches or unauthorized access cannot be eliminated.

To mitigate these risks, survey items have been restricted to the minimum necessary to achieve the study objectives. All research procedures will comply with national and institutional information security guidelines. Only devices with up-to-date security software will be used; temporary cloud-stored data will be promptly deleted; and all data will be stored in encrypted form and accessed exclusively by authorized researchers.

Participants who experience psychological distress during or after the study may contact the survey company’s consultation service or the research team directly. Participation will be voluntary, and participants may withdraw at any time. Responses will be analyzed only if the survey is completed and formally submitted.

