Third, a more fundamental limitation of the cross-sectional design is the inability to distinguish state from trait (e.g., whether poor sleep is a cause or a consequence of depression) and the inability to infer causal directionality in mediation models. All mediation analyses and structural equation modeling (SEM) models employed across the registry should be interpreted with caution, as the relations identified reflect statistical associations only and do not support causal inference. Indeed, cross-sectional mediation analyses yield biased estimates of longitudinal indirect effects [100]. The moderated mediation analyses in Sub-study 1d are subject to the same constraint and can only characterize conditional association patterns, not causal mediation. Therefore, the findings should be interpreted as hypothesis-generating evidence to be examined in future longitudinal designs.

Finally, although several measures were implemented to minimize careless responding before data collection, including a quality-check pledge item and built-in logic and consistency checks, the identification of inattentive responding in clinical populations presents methodological challenges. Commonly used detection indices, such as longstring analysis, Mahalanobis distance, and intra-individual response variability, may be confounded with respondents’ characteristics and genuine response tendencies, making it difficult to determine whether flagged responses reflect genuine inattention or valid patterns of responding [92,101]. Accordingly, the potential presence of residual inattentive responding cannot be ruled out as a source of measurement error in the present data.

Looking ahead, the TAMS registry may provide a foundation for future longitudinal extensions. Subject to funding, ethics approval, and the operational feasibility of panel re-contact through the survey provider, a follow-up wave could be considered using an abbreviated core-PROs battery to reduce respondent burden while preserving the main cross-domain constructs. In addition, FAIR-aligned release of the baseline dataset may facilitate harmonization or comparative use alongside independent longitudinal datasets. Such extensions could help examine temporal ordering more directly, evaluate the stability of transdiagnostic profiles over time, and characterize longitudinal changes in attitudes toward digital health technology.

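### The listed sensitivity analyses for a 110-minute forced-response survey do not vary response quality, although careless answers can inflate as well as attenuate associations

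*Protocol article*

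**What the plan says.** Burden. Section 2.4: "The survey consists of 1–40 items per page across 45 pages, and all items are mandatory". Section 2.9: "Completion of the self-administered questionnaires (approximately 110 minutes in total) may impose a time burden on participants". Section 2.3: "Participants who complete the survey will receive points equivalent to 200 yen".

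Safeguards before and during the survey (section 2.8). At the start, "participants will be presented with a pledge item asking them to commit to responding carefully". The platform adds forced response, built-in logic and consistency checks, duplicate prevention and a 24-hour upper limit on completion. No lower limit on completion time is stated.

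Safeguards after collection. Section 2.7: "To minimize information bias, we will conduct logic and range checks during data cleaning". The sensitivity analyses listed there vary scoring or short forms, thresholds, non-linear terms and clustering parameters. Table 1 adds outlier identification for Sub-study 1b, not described as a screen for careless answers, and unspecified sensitivity analyses for 1b, 1c and 1d.

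Limitation. The Discussion names longstring, Mahalanobis distance and intra-individual response variability, says they may be confounded with genuine response tendencies, and concludes that "the potential presence of residual inattentive responding cannot be ruled out as a source of measurement error in the present data".

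**The concern.** An answer to a closed rating item is in range whatever the respondent's attention. Logic and consistency checks across items can be failed, but they are not built to catch random or same-column answers within a scale. The article then gives the ambiguity of the detection indices as the difficulty and stops. That ambiguity is a good reason not to delete flagged records from the main analysis. It is no reason to omit a comparison with and without them.

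Direction matters too. The two preceding limitations discuss which way selection and diagnostic misclassification may bias results; the one on inattention does not. A reader will tend to take measurement error as noise that weakens associations. Yet if attentive respondents score low on two scales, random responders score well above them on both, and this induces a positive correlation between the scales. The Benjamini–Hochberg control planned in 1b and 1c does not remove it, because the correlation is real in the mixed sample. In Aim 2, careless respondents could also form a cluster that is high on every measure; that possibility is not quantified here.

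**Working it through.** **1. The protocol's own yardstick (section 2.6).** Assume two-sided 5% and 80% power, neither of which the article states. Detectable r = tanh[(1.96 + 0.84)/√(n − 3)].
- n = 200: 0.197
- n = 300: 0.161

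This reproduces the stated 0.20 to 0.16. The half-widths (6.93%, 5.66%) and d (0.280, 0.229) reproduce as well.

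**2. Formula.** Let a share c answer carelessly, with careless-minus-attentive mean gaps dx and dy:

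r = [(1−c)·ρ·sx·sy + c·rc·scx·scy + c(1−c)·dx·dy] / √(Vx·Vy), with Vx = (1−c)·sx² + c·scx² + c(1−c)·dx², and Vy likewise.

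Here ρ is the true correlation, rc the correlation among careless respondents, and s and sc the attentive and careless SDs.

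**3. Low-scoring scales, random answering, ρ = 0.** Assumed scales: 9 and 7 items scored 0–3, item loading 0.7, cumulative category shares 0.65/0.88/0.96. Simulated attentive means are 4.6 of 27 (SD 4.87) and 3.6 of 21 (SD 3.86). Random answers have means 13.5 and 10.5 and variances 9 × 1.25 = 11.25 and 7 × 1.25 = 8.75. The gaps are therefore about 8.9 and 6.9, and rc = 0.
- c = 10%: covariance 0.09 × 8.9 × 6.9 ≈ 5.5; variances ≈ 29.5 and 18.6; r ≈ 5.5/√(29.5 × 18.6) ≈ 0.24.
- c = 5%: covariance ≈ 2.9; variances ≈ 26.7 and 16.8; r ≈ 0.14.
- c = 15%: r ≈ 0.31.

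Item-level simulation agrees. Straight-lining the same column on both scales gives 0.28 at 5% and 0.44 at 10%.

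**4. False-positive rates.** Two unrelated 9-item scales, attentive mean 17.5% of range, nominal 5% test, 2,000 replicates, random answering:

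| Careless | Mean r | n = 200 | n = 300 |
|---|---|---|---|
| 5% | 0.13 | 44% | 60% |
| 10% | 0.225 | 88% | 97% |

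**5. Where inflation shrinks, vanishes or reverses (ρ = 0, 5% and 10% careless).**
- Random answering, attentive means about 33% of range: r about 0.03 and 0.05.
- Random answering, scales centred at mid-range: about zero.
- Straight-lining, scales centred at mid-range: about 0.09 and 0.18 (0.10 and 0.20 with two 9-item scales).
- Random answering, means at 25% and 75% of range, SD 18% attentive and 10% careless: r = −0.09 and −0.16.

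**6. A true correlation of 0.30, random answering by 5% and 10%, same SDs.** With both means at 25% of range, the observed r rises to 0.36 and 0.40. On centred scales it falls to about 0.29.

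**7. Would a check help?** If a random responder passes a four-option instructed item one time in four, the chance of failing at least two of three is 1 − 3(0.25²)(0.75) − 0.25³ = 0.84. Starting from 10% careless, the share left is 0.0156/(0.90 + 0.0156) = 1.7%, and r in step 3 drops from 0.24 to about 0.05.

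**The case against.** Several stronger readings are tempting and fail. A reader might infer that logic and range checks are the only defence, or that closed-response data cannot fail any check. The article also has the pledge, in-survey consistency checks and, in 1b, outlier identification; only range checks are unfailable for closed items. Full specifications are left to Supplementary Materials not shown here, so the contents of the 1b–1d sensitivity analyses are unknown. The point therefore rests on the list in section 2.7 and the limitation as written.

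A reader might also infer that the authors dismiss the residue as harmless noise, or reject the indices outright. They do neither: the limitation says the indices may be confounded, and measurement error can be systematic. It is incomplete, not false.

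Nor do the documents show that 1b and 1d are biased towards confirmation. Sub-study 1b enrols patients only, and no score distributions are given for its scales or for those in 1d. Inflation needs low means on both scales or a shared response style.

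Instructed-response items are not free of the authors' worry either. ADHD and autism are target groups, so failures may track diagnosis. Collection was planned for March 2026, so items can be added only if the survey has not been fielded. The burden is openly acknowledged and partly mitigated by short forms, selected subscales and pause-and-resume.

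All of this limits the claim. None of it explains why a with-and-without comparison that deletes nobody from the main analysis is not among the listed sensitivity analyses.

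**Conclusion.** The point holds as a cheap improvement. In the text shown, the general safeguards would largely miss random or straight-lined answers within a scale, and the listed sensitivity analyses do not vary response quality. The limitation gives no direction for a bias that can go either way. At an assumed 5% to 10% careless, spurious correlations on low-scoring scales reach the size the protocol treats as detectable; on mid-range scales only straight-lining produces them. The careless share, the score distributions and the response style are all assumptions, so these figures show what could happen, not what will.

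**What to change.** 1. Keep all respondents in the main analysis. Add to the sensitivity analyses in section 2.7 one prespecified rerun of each confirmatory sub-study and of the Aim 2 clustering, excluding flagged respondents.
2. If the survey is not yet fielded, place three instructed-response items early, midway and late, with different correct columns so that a straight-liner cannot pass them all. Flag those failing two or more.
3. If it is already fielded, flag by data-derived indices such as longstring, and by completion time if the panel provider supplies it. Longstring finds straight-lining but not random answering, so say which type each flag addresses.
4. Report flag rates by diagnostic stratum, because failures may reflect ADHD or other attention problems.
5. Reword the limitation to say that residual inattention can inflate as well as attenuate associations.

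Cost: under a minute of extra items, one rerun per sub-study, and some genuine respondents flagged in the sensitivity analysis only.

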## 4. Conclusions

This protocol describes the establishment of a multidimensional PROs registry designed to provide a unified framework for evaluating patient-relevant outcomes in mental health. By enabling the concurrent assessment of QOL and psychosocial factors, psychiatric symptoms, sleep characteristics, and attitudes toward digital health technology using a standardized measurement system, the registry addresses the key limitations of prior research in which these domains have typically been examined in isolation.

## Data Availability

Since this article describes the protocol for the TAMS registry, no individual-level dataset is available at the time of publication. The data will be available from the corresponding author upon reasonable request.

## Abbreviations

APSQ, Anxiety and Preoccupation about Sleep Questionnaire; ASSURE-HT and ASSURE-AI, Attitudes toward Safety, Support, Understanding, and Risk for Human-AI Therapists; AQ-28, short form of the Autism Spectrum Quotient; ASI-3, Anxiety Sensitivity Index-3; ASRS, Adult ADHD Self-Report Scale; BPBs, Brief Parental Burnout Scale; BPS, Bedtime Procrastination Scale; CAS-1R, Cognitive Attentional Syndrome Scale-1 Revised; DBAS-16, Dysfunctional Beliefs and Attitudes about Sleep Scale; DQ5-J, Japanese version of the Distress Questionnaire-5; DRR, Desire for Real-World Relationships; EC, Effortful Control Scale; eHEALS, eHealth Literacy Scale; eTAP-J, Japanese version of the e-Therapy Attitudes and Process Questionnaire; EQ-5D-5L, EuroQol 5 Dimensions 5-Level; FAIR, Findable, Accessible, Interoperable, and Reusable; FIRST, Ford Insomnia Response to Stress Test; GAD-7, Generalized Anxiety Disorder 7-item Scale; IES-R, Impact of Event Scale-Revised; ISI, Insomnia Severity Index; K6, six-item Kessler Psychological Distress Scale; LSAS, Liebowitz Social Anxiety Scale; MCQ-30, short form of the Metacognitions Questionnaire; OCI-R, Obsessive/Compulsive Inventory-Revised; PHQ-9, Patient Health Questionnaire-9; PROs, Patient-Rreported Outcomes; QOL, Quality of Life; RA, Relationship Authenticity; rMEQ, Reduced Morningness–Eveningness Questionnaire; RU-SATED, Regularity, Satisfaction, Alertness, Timing, Efficiency, Duration of Sleep Scale; SAP, Shift-and-Persist coping strategy; SES, Subjective Socioeconomic Status (Childhood and Current); SHPS, Sleep Hygiene Practice Scale; SWLS, Satisfaction With Life Scale.
